**Randomization**

Based on whether the enrolled study participants have received any type of flu shot within the past 3 months, the participants will be classified as influenza vaccine recipients and non-recipients. Within each category, they will be randomly assigned to the control group or treatment group. The assignment will be balanced so that equal numbers are assigned to each group.

**Interim Analysis**

We will carry out an interim analysis when all the patients recruited have been followed for one and a half months. Since this is a pilot study, this analysis will be carried out at a stringent level of significance.

**Statistical Analysis**

Standard techniques of descriptive statistics will be used to compare demographics and other patient characteristics in the two treatment groups. Since an additional focus of this pilot study is to obtain accurate estimates of the moments of the distributions of the outcome variables, confidence intervals will also be provided. Descriptive summaries of the number of events and duration of infection will be generated for the two groups. As stated above, the t-test will be used to compare estimates of the average number of events per person as well as the average duration of illness between the two groups. To the extent that the small sample size allows it, we will utilize regression techniques for count data, using SAS GENMOD, to model the number of events per person adjusting for relevant covariates.

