**Protocol Schema**

A Pilot Study of the Safety, Tolerability, and Effectiveness of Halo to Prevent Acute Upper Respiratory Illness and Respiratory Virus Infections

**DESIGN** This is a randomized, double-blinded, placebo-controlled clinical trial

**DURATION** Participants will be on treatment for 75 days. A follow up visit will occur within 2 months after treatment ends.

**SAMPLE SIZE** 51 participants each in the treatment and placebo arms

**POPULATION** Healthy men and women 18 to 45 years old, inclusive

**INTERVENTION** Participants will be randomized with equal proportion (51 each) into one of the following 2 groups:

- Halo administered intra-orally by spray Three times daily
- Placebo administered intra-orally by spray Three times daily

**HYPOTHESIS** The use of Halo sprayed intra-orally three times daily

will be associated with fewer episodes and duration of acute

respiratory diseases and less frequent detection of important

respiratory viruses confirmed by multiplex PCR

**PRIMARY OBJECTIVES** 1. To establish whether Halo will decrease the

frequency of acute upper respiratory illness

2. To assess whether Halo will decrease the duration

and severity of acute upper respiratory illness

**SECONDARY**  1. To assess the tolerability, acceptability and adherence to

**OBJECTIVES** Halo

2. To compare whether acute upper respiratory disease in

those receiving Halo compared to placebo is associated with differences in absenteeism (from work or school) and visits to physicians’ offices, emergency departments and urgent care centers

3. To determine whether Halo will decrease

the detection of respiratory viruses by PCR

4. To evaluate the effect of Halo on bacterial and fungal

microflora in the oropharynx

5. To evaluate the effect of Halo on those who did and did not receive the influenza vaccine.

**ENDPOINTS** 1. Frequency and duration of clinical respiratory disease at

interim visits and assisted by patient diaries

2. Intra-and extra-oral exams

3. Solicited and unsolicited adverse events

4. Respiratory virus multiplex PCR

5. Bacterial (oral streptococci, Group A streptococcus) and

fungal cultures

6. Bottle counts and self-report for adherence

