**Selection and enrollment of participants**

**Study Enrollment and Withdrawal**

One hundred two healthy male and female participants, ages 18-45 will be enrolled in two groups. It is estimated that 204 subjects will need to be screened (2:1 screened to eligible) to enroll 102 subjects. At screening/enrollment, subjects will be stratified as to whether they received inactivated or live influenza virus vaccination. Subjects will be recruited through customary IRB-approved methods. Children, pregnant women, prisoners and other vulnerable individuals will not be enrolled.

Screening will begin with a brief IRB-approved telephone screen. Information about the study will be presented to potential subjects. The telephone script will include the inclusion/exclusion criteria. Appointments will be made for subjects who are interested in the study at the Case Western Reserve University Dental School Room 3080 for further screening/enrollment procedures and protocol-specific information.

Study retention strategies will include education and explanations of the study schedule and procedures during enrollment. In addition, reimbursements will be dispersed at specified time points during the study with the amount contingent on completion of study procedures. Participants will be reminded before visits, and the clinical research study staff will contact participants who miss appointments to determine if they wish to return for further evaluation.

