**Study Outcome Measures**

The **primary study objective** is to establish whether Halo will decrease the frequency, duration, and severity of acute respiratory disease and decrease the detection of respiratory viruses by multiplex PCR. After enrollment, subjects will be seen at scheduled monthly visits (+/- 7 days), 1-2 months after study completion and at interim visits when they develop a syndrome consistent with an acute upper respiratory disease. An acute upper respiratory disease will be defined as having fever to > 37.8°C and a non-productive cough and 2 or more of the following symptoms:

- Sore throat
- Rhinorrhea
- Sinus congestion
- Malaise

Patients will be provided with diaries (RedCap) to note any illness especially acute respiratory disease and to record the duration of each sign or symptom. Subjects will also be asked to take their temperature at 5p.m. each day and record their temperatures in the diaries. At interim visits related to the development of acute upper respiratory illness oropharyngeal swabs will be obtained for bacterial and fungal culture as well as respiratory virus multiplex PCR.

**Multiplex RT-PCR:** Following collection, an aliquot of the clinical sample will be placed in viral freezing media and stored at -80 degrees. Samples will be placed in 2ml glass collection tubes at a 1:1 ratio of clinical sample to viral freezing media. RNA from each clinical specimen will be extracted with the QiaAmp Viral RNA Mini Kit (Qiagen Inc., Valencia, CA) according to the manufacturer’s protocol. Extracted RNA will be stored at -80 degrees until processing.

Primers and probe sets for multiplex real-time RT-PCR detection of respiratory tract viruses have already been described [[35](#_ENREF_35)]. We will screen influenza positive samples under conditions as described with the exception that chlamydia and mycoplasma primer sets will be omitted. In addition, screening reactions for recently recognized viruses will be performed separately using real time primer sets as previously described [[36](#_ENREF_36), [37](#_ENREF_37)].

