**Statistical Analysis**

**Sample Size Calculations**

Initially, primary outcomes in the control group vs. the treatment group will be compared using the t-test for independent samples, and this technique was used to estimate sample sizes. Specifically, sample size calculations were carried out assuming that the two groups will be of equal size and that the random assignment will be balanced. Further, it was assumed that an average of 2 events would occur in the control group, contrasted against an average of 1.5 events in the treated group (SD = 1), and that the average duration of illness would be 4 days and 3 days in the control and treated groups, respectively (SD = 2). Taking alpha to be 0.05, a sample size of 23 per group would allow the detection of a 25% difference in primary outcomes between the two groups with 80% power. The sample size was increased to 51 per group to account for potential losses to follow-up.

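### The primary frequency comparison is an unadjusted t-test on raw event counts, with no allowance for days observed or the randomisation stratum, so unequal dropout can bias it in either direction

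*Protocol*

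**What the plan says.** - **Test.** Protocol, Sample Size Calculations: "primary outcomes in the control group vs. the treatment group will be compared using the t-test for independent samples". The Statistical Analysis section repeats this for frequency: "the t-test will be used to compare estimates of the average number of events per person". Neither section mentions follow-up time or the stratum.
- **Supplementary model.** Protocol, Statistical Analysis: "To the extent that the small sample size allows it, we will utilize regression techniques for count data, using SAS GENMOD". The covariates for this model are not listed. The model is conditional. It names neither a follow-up offset nor vaccine status.
- **Stratum.** Protocol, Randomization: "Based on whether the enrolled study participants have received any type of flu shot within the past 3 months", participants are classed as recipients or non-recipients and randomised within class. Study Enrollment and Withdrawal says "subjects will be stratified as to whether they received inactivated or live influenza virus vaccination", with no time window.
- **Early exit.** Sample Size Calculations raises 23 to 51 per group for losses. Randomization and Withdrawal Procedures makes withdrawal mandatory after a grade 3 or 4 adverse event. Screening/Enrollment lets participants start product before laboratory results are known and discontinues those with excluding values.
- **Counting period.** Protocol Schema: "Participants will be on treatment for 75 days". Study Outcome Measures: "subjects will be seen at scheduled monthly visits (+/- 7 days". Appendix 2 lists three follow-up visits, with product dispensed at enrolment and at the first two. Scheduled Follow-up Visits supplies product until the next visit.

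**The concern.** A participant observed for half the period has about half the chance to record an episode, yet the t-test treats that count as complete. If one arm loses more participants, or loses them earlier, its mean falls for reasons unrelated to efficacy.

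Unequal loss is plausible here. Halo contains an antiseptic and flavours, while placebo is purified water. Appendix 1 grades a taste change lasting over an hour as grade 3, which triggers mandatory withdrawal. The documents do not say which arm will lose more.

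The stratum is a separate matter. Randomising within vaccine category and then analysing without it leaves a standard error that does not match the design.

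**Working it through.** **The plan's own figures.** The protocol gives no figure for this bias. Its one related figure is 23 per group, raised to 51. The stated inputs (2 against 1.5 events, SD 1) give a standardised difference of 0.5, and 2(1.960 + 0.842)²/0.5² = 63 per group two-sided, so 23 is not reproduced. That is a separate matter. Read as n/(1 − d), the increase allows a loss of 1 − 23/51 = 55%.

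**Unequal dropout, no true effect.** From the protocol: control mean 2 and 51 per arm. Assumed: Poisson counts, leavers exit half-way, and the dropout proportions d shown. With f the observed fraction (1 or 0.5):

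- mean = 2(1 − 0.5d)
- variance = mean + 4·Var(f), with Var(f) = 0.25·d(1 − d)
- SE = √[(V_Halo + V_placebo)/51]
- two-sided error = Φ(−1.96 + δ/SE) + Φ(−1.96 − δ/SE), where δ is the difference in means

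| Dropout, Halo / placebo | Mean, Halo / placebo | Ratio | δ | Variances | SE | Error by formula | Error by simulation |
|---|---|---|---|---|---|---|---|
| 20% / 5% | 1.80 / 1.95 | 0.923 | 0.15 | 1.96, 1.9975 | 0.279 | 8.4% | 8.2-8.5% |
| 40% / 10% | 1.60 / 1.90 | 0.842 | 0.30 | 1.84, 1.99 | 0.274 | 19.5% | 18.5-19% |

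In simulation, a false finding in favour of Halo occurs in 7.6% and 18.9% of trials, against a nominal 2.5%.

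**Other directions** (20,000 simulated trials each, exit time uniform over the period):

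- No dropout: error 5.2%. Equal 20% dropout: error 4.9%.
- Equal 20% dropout with a true effect: the difference shrinks from 0.50 to 0.9 × 0.50 = 0.45, and power falls from 47% to 40%.
- Placebo 30%, Halo 10%, no true effect: shift of −0.20 events, and false benefit falls to 0.4%.
- Placebo 25%, Halo 5%, true means 2 and 1.5: expected difference 1.75 − 1.4625 = 0.29, and power is about 19%. A person-time analysis has 45%.
- With no true effect, the person-time analysis keeps the error at 4.7-5.1% and the rate ratio at about 1.00 in every scenario. Exit is unrelated to illness risk in all of them.

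**Ignoring the stratum.** Assumed: half of participants vaccinated, no dropout, and the vaccine rate ratios shown. Power is for a true 25% reduction.

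| Vaccine rate ratio | Error, unadjusted t-test | Power, unadjusted |
|---|---|---|
| 1 | 5.1% | 47% |
| 0.8 | 4.6% | 46% |
| 0.6 | 3.9% | 43% |
| 0.4 | 2.2% | 36% |

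Adjusting for the stratum keeps the error near 5% and power at about 47% throughout.

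**Counting window.** Appendix 2 gives no visit days. If a month is 30 days, the third visit falls at 90 ± 7 = 83 to 97 days, against 75 days of treatment. 90/75 = 1.20, so expected counts would be 20% higher in both arms (2.4 rather than 2.0 on placebo), and the ratio between arms is unchanged.

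**The case against.** A reader might infer that early dropout in this trial will look like benefit. The documents do not support that. They give no dropout rate by arm and no expected direction, and the safety sections describe an acceptable profile. False benefit needs greater or earlier loss on Halo.

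Withdrawal is also not always loss of observation. Randomization and Withdrawal Procedures asks withdrawn participants to permit continued scheduled evaluations and an end-of-study evaluation. This lessens the problem. It does not remove it, because continuation is voluntary and meant for safety.

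It would also be wrong to count the other points as sources of false benefit. Ignoring the stratum works the other way, and the window conflict applies to both arms. The three-month vaccine window can be read as refining the enrolment section, so it is not a clear contradiction.

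Finally, this is a pilot, the t-test is described as an initial comparison, and a SAP could supply the offset and covariates of the count model. That would excuse silence on those details. It does not excuse a named primary test that omits both features, with the better model left conditional on sample size. The protocol's own means imply 51 × 2 + 51 × 1.5 = 178.5 events with full follow-up, enough for arm and one binary stratum.

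**Conclusion.** The concern holds in limited form. The stated primary test for frequency ignores observation time, and differential dropout would bias it in whichever direction the dropout falls. With markedly greater loss on Halo, type I error rises from 5% to about 8%, or to 18-19% in the more extreme case. With greater loss on placebo, a real benefit is masked. These sizes rest on assumed dropout, Poisson counts and exit unrelated to illness. Counts less variable than Poisson, such as the protocol's SD of 1, would make the same shift weigh more: 0.15/√(2/51) = 0.76 standard errors rather than 0.15/0.279 = 0.54.

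Omitting the stratum is a smaller, separate loss of efficiency, about 1 to 4 points of power at vaccine rate ratios of 0.8 to 0.6. The window and vaccine wording are consistency points and carry no demonstrated bias.

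**What to change.** - **Primary frequency analysis.** Use a Poisson or negative-binomial regression, in the GENMOD procedure already named, of episode count on arm and the vaccine stratum as randomised, with offset log(days observed) and robust variance. Include all randomised participants with at least one observed day, since the offset is undefined at zero. Report the rate ratio with its 95% CI and keep the t-test as a sensitivity analysis.
- **Stated limits.** Say that the offset removes bias only if leaving is unrelated to illness risk, and that it assumes a steady rate over follow-up in a seasonal disease. Duration, compared by the same t-test, is not covered by this change.
- **Counting window.** Reconcile the 75-day treatment period in the Protocol Schema with the monthly visits and dispensing schedule (Study Outcome Measures, Scheduled Follow-up Visits, Appendix 2), so that one counting window applies to everyone.
- **Vaccine status.** Reconcile the wording in Study Enrollment and Withdrawal with that in Randomization.

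**Cost.** Protocol and SAP wording only, with no new data collection. The downside is that the effect measure becomes a rate ratio while the trial is sized on a mean difference, so the sample-size section would need restating on the new scale.

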APPENDIX 1: TOXICITY TABLE

**DMID Adult Toxicity Table, November 2007**

**ABBREVIATIONS:** Abbreviations utilized in the Table:

ULN = Upper Limit of Normal LLN = Lower Limit of Normal

R_x_ = Therapy Req = Required

Mod = Moderate IV = Intravenous

ADL = Activities of Daily Living Dec = Decreased

**ESTIMATING SEVERITY GRADE**

For abnormalities NOT found elsewhere in the Toxicity Tables use the scale below to estimate grade of severity:

**GRADE 1 Mild –** Transient or mild discomfort (< 48 hours); no medical intervention/therapy required

**GRADE 2 Moderate –** Mild to moderate limitation in activity - some assistance may be needed; no or minimal medical intervention/therapy required

**GRADE 3 Severe** **–** Marked limitation in activity, some assistance usually required; medical intervention/therapy required, hospitalizations possible

**GRADE 4 Life-threatening** – Extreme limitation in activity, significant assistance required; significant medical intervention/therapy required, hospitalization, or hospice care probable

**SERIOUS OR LIFE-THREATENING AEs**

ANY clinical event deemed by the clinician to be serious or life threatening should be considered a grade 4 event. Clinical events considered serious or life threatening include, but are not limited to: seizures, coma, tetany, diabetic ketoacidosis, disseminated intravascular coagulation, diffuse petechiae, paralysis, acute psychosis, and severe depression.

| **HEMATOLOGY** | | | | |
| --- | --- | --- | --- | --- |
|  | Grade 1 | Grade 2 | Grade 3 | Grade 4 |
| Hemoglobin | 9.5 - 10.5 gm/dL | 8.0 - 9.4gm/dL | 6.5 - 7.9 gm/dL | < 6.5 gm/dL |
| Absolute Neutrophil Count | 1000-1500/mm^3^ | 750-999/mm^3^ | 500-749/mm^3^ | <500/mm^3^ |
| Platelets | 75,000-99,999/mm^3^ | 50,000-74,999/mm^3^ | 20,000-49,999/mm^3^ | <20,000/mm^3^ |
| WBCs | 11,000-13,000/ mm^3^ | 13,000-  15,000 /mm^3^ | 15,000-  30,000/mm^3^ | >30,000 or <1,000 /mm^3^ |
| % Polymorphonuclear Leucocytes + Band Cells | > 80% | 90 – 95% | >95% |  |
| Abnormal  Fibrinogen | Low:  100-200 mg/dL  High:  400-600 mg/dL | Low:  <100 mg/dL  High:  >600 mg/dL | Low:  < 50 mg/dL | Fibrinogen associated with gross bleeding or with disseminated coagulation |
| Fibrin Split Product | 20-40 mcg/mL | 41-50 mcg/mL | 51-60 mcg/mL | > 60 mcg/mL |
| Prothrombin  Time (PT) | 1.01 - 1.25 x ULN | 1.26-1.5 x ULN | 1.51 -3.0 x ULN | >3 x ULN |
| Activated Partial Thromboplastin (APPT) | 1.01 - 1.66 x ULN | 1.67 - 2.33 x ULN | 2.34 - 3 x ULN | > 3 x ULN |
| Methemoglobin | 5.0 - 9.9 % | 10.0 - 14.9 % | 15.0 - 19.9% | > 20.0 % |

| **CHEMISTRIES** | | | | |
| --- | --- | --- | --- | --- |
|  | Grade 1 | Grade 2 | Grade 3 | Grade 4 |
| Hyponatremia | 130-135 mEq/L | 123-129 mEq/L | 116-122 mEq/L | < 116 mEq/L or abnormal sodium *with* mental status changes or seizures |
| Hypernatremia | 146-150 mEq/L | 151-157 mEq/L | 158-165 mEq/L | > 165 mEq/L or abnormal sodium *with* mental status changes or seizures |
| Hypokalemia | 3.0 - 3.4 mEq/L | 2.5 - 2.9 mEq/L | 2.0 - 2.4 mEq/L  or intensive replacement therapy or hospitalization required | < 2.0 mEq/L or abnormal potassium *with*  paresis, ileus, or life-threatening arrhythmia |
| Hyperkalemia | 5.6 - 6.0 mEq/L | 6.1 - 6.5 mEq/L | 6.6 - 7.0 mEq/l | > 7.0 mEq/L  or abnormal potassium *with* life-threatening arrhythmia |
| Hypoglycemia | 55-64 mg/dL | 40-54 mg/dL | 30-39 mg/dL | <30 mg/dL or abnormal glucose *with* mental status changes or coma |

| **CHEMISTRIES (continued)** | | | | |
| --- | --- | --- | --- | --- |
|  | Grade 1 | Grade 2 | Grade 3 | Grade 4 |
| Hyperglycemia  (nonfasting and no prior diabetes) | 116 - 160 mg/dL | 161- 250 mg/dL | 251 - 500 mg/dL | > 500 mg/dL or abnormal glucose *with* ketoacidosis  or seizures |
| Hypocalcemia  (corrected for albumin) | 8.4 - 7.8 mg/dL | 7.7 - 7.0 mg/dL | 6.9 - 6.1 mg/dL | < 6.1 mg/dL  or abnormal calcium *with* life threatening arrhythmia or tetany |
| Hypercalcemia  (correct for albumin) | 10.6 - 11.5 mg/dL | 11.6 - 12.5 mg/dL | 12.6 - 13.5 mg/dL | > 13.5 mg/dL or abnormal calcium *with* life  threatening  arrhythmia |
| Hypomagnesemia | 1.4 - 1.2 mEq/L | 1.1 - 0.9 mEq/L | 0.8 - 0.6 mEq/L | < 0.6 mEq/L or abnormal magnesium *with* life-threatening arrhythmia |
| Hypophosphatemia | 2.0 - 2.4 mg/dL | 1.5 -1.9 mg/dL or  replacement Rx required | 1.0 -1.4 mg/dL  intensive therapy  or  hospitalization required | < 1.0 mg/dL or abnormal phosphate *with* life-threatening arrhythmia |
| Hyperbilirubinemia (when accompanied by any increase in other liver function test) | 1.1 - <1.25 x ULN | 1.25 - <1.5 x ULN | 1.5 – 1.75 x ULN | > 1.75 x ULN |

| **CHEMISTRIES (continued)** | | | | |
| --- | --- | --- | --- | --- |
|  | Grade 1 | Grade 2 | Grade 3 | Grade 4 |
| Hyperbilirubinemia (when other liver function are in the normal range) | 1.1 - <1.5 x ULN | 1.5 - <2.0 x ULN | 2.0 – 3.0 x ULN | > 3.0 x ULN |
| BUN | 1.25 - 2.5 x ULN | 2.6 - 5 x ULN | 5.1 - 10 x ULN | > 10 x ULN |
| Hyperuricemia (uric acid) | 7.5 – 10.0 mg/dL | 10.1 – 12.0 mg/dL | 12.1 – 15.0 mg/dL | >15.0 mg/dL |
| Creatinine | 1.1 - 1.5 x ULN | 1.6 - 3.0 x ULN | 3.1 - 6 x ULN | > 6 x ULN or  dialysis required |

| **ENZYMES** | | | | |
| --- | --- | --- | --- | --- |
|  | Grade 1 | Grade 2 | Grade 3 | Grade 4 |
| AST (SGOT) | 1.1 - <2.0 x ULN | 2.0 – <3.0 x ULN | 3.0 – 8.0 x ULN | > 8 x ULN |
| ALT (SGPT) | 1.1 - <2.0 x ULN | 2.0 – <3.0 x ULN | 3.0 – 8.0 x ULN | > 8 x ULN |
| GGT | 1.1 - <2.0 x ULN | 2.0 – <3.0 x ULN | 3.0 – 8.0 x ULN | > 8 x ULN |
| Alkaline Phosphatase | 1.1 - <2.0 x ULN | 2.0 – <3.0 x ULN | 3.0 – 8.0 x ULN | > 8 x ULN |
| Amylase | 1.1 - 1.5 x ULN | 1.6 - 2.0 x ULN | 2.1 - 5.0 x ULN | > 5.1 x ULN |
| Lipase | 1.1 - 1.5 x ULN | 1.6 - 2.0 x ULN | 2.1 - 5.0 x ULN | > 5.1 x ULN |

| **CARDIOVASCULAR** | | | | |
| --- | --- | --- | --- | --- |
|  | Grade 1 | Grade 2 | Grade 3 | Grade 4 |
| Cardiac Rhythm |  | asymptomatic, transient signs, no  Rx required | recurrent/persistent;  symptomatic Rx required | unstable dysrhythmia; hospitalization and treatment required |
| Hypertension | transient increase  > 20 mm/Hg; no treatment | recurrent, chronic increase  > 20mm/Hg;  treatment required | acute treatment required; outpatient treatment or hospitalization possible | end organ damage or hospitalization required |

| **CARDIOVASCULAR** | | | | |
| --- | --- | --- | --- | --- |
|  | Grade 1 | Grade 2 | Grade 3 | Grade 4 |
| Hypotension | transient orthostatic hypotension with heart rate increased by <20 beat/min or decreased by <10 mm Hg systolic BP; no treatment required | symptoms due to orthostatic hypotension or BP decreased by <20 mm Hg systolic; correctable with oral fluid treatment | requires IV fluids; no hospitalization required | mean arterial pressure  <60mm/ Hg or end organ damage or shock; requires hospitalization and vasopressor treatment |
| Pericarditis | minimal effusion | mild/moderate asymptomatic effusion; no treatment | symptomatic effusion; pain; EKG changes | tamponade; pericardiocentesis or surgery required |
| Hemorrhage, Blood Loss | microscopic/occult | mild, no transfusion | gross blood loss;  1-2 units transfused | massive blood loss; > 3 units transfused |

| **GASTROINTESTINAL** | | | | |
| --- | --- | --- | --- | --- |
|  | Grade 1 | Grade 2 | Grade 3 | Grade 4 |
| Nausea | mild or transient; maintains reasonable intake | moderate discomfort; intake decreased significantly; some activity limited | no significant intake; requires IV fluids | hospitalization required; |
| Vomiting | 1 episode in 24 hours | 2-5 episodes in 24 hours | >6 episodes in 24 hours or needing IV fluids | physiologic consequences requiring hospitalization or requiring parenteral nutrition |
| Constipation | requiring stool softener or dietary modification | requiring laxatives | obstipation requiring manual evacuation or enema | obstruction or toxic megacolon |
| Diarrhea | mild or transient; 3-4 loose stools/day or mild diarrhea last < 1 week | moderate or persistent; 5-7 loose stools/day or diarrhea lasting >1 week | >7 loose stools/day or bloody diarrhea; or orthostatic hypotension or electrolyte imbalance or >2L IV fluids required | hypotensive shock or physiologic consequences requiring hospitalization |
| Oral Discomfort/Dysphagia | mild discomfort; no difficulty swallowing | some limits on eating/drinking | eating/talking very limited; unable to swallow solid foods | unable to drink fluids; requires IV fluids |
| **NEUROLOGICAL** | | | | |
|  | Grade 1 | Grade 2 | Grade 3 | Grade 4 |
| Neuro-Cerebellar | slight incoordination dysdiadochokinesis | intention tremor, dysmetria, slurred speech; nystagmus | locomotor ataxia | incapacitated |
| Psychiatric | mild anxiety or depression | moderate anxiety or depression; therapy required; change in normal routine | severe mood changes requiring therapy; or suicidal ideation; or aggressive ideation | acute psychosis requiring hospitalization; or suicidal gesture/attempt; or hallucinations |
| Muscle Strength | subjective weakness  no objective symptoms/ signs | mild objective  signs/symptoms  no decrease in function | objective weakness function limited | paralysis |
| Paresthesia (burning, tingling, etc.) | mild discomfort; no treatment required | moderate discomfort; non-narcotic analgesia required | severe discomfort; or narcotic analgesia required with symptomatic improvement | incapacitating; or not responsive to narcotic analgesia |

| **NEUROLOGICAL** | | | | |
| --- | --- | --- | --- | --- |
|  | Grade 1 | Grade 2 | Grade 3 | Grade 4 |
| Neuro-sensory | mild impairment in sensation (decreased sensation, e.g., vibratory, pinprick, hot/cold in great toes) in focal area or symmetrical distribution; or change in taste, smell, vision, and/or hearing | moderate impairment (mod decreased sensation, e.g., vibratory, pinprick, hot/cold to ankles) and/or joint position or mild impairment that is not symmetrical | severe impairment (decreased or loss of sensation to knees or wrists) or loss of sensation of at least mod degree in multiple different body areas (i.e., upper and lower extremities) | sensory loss involves limbs and trunk; paralysis; or seizures |

| **MUSCULOSKELATEL** | | | | |
| --- | --- | --- | --- | --- |
|  | Grade 1 | Grade 2 | Grade 3 | Grade 4 |
| Arthralgia  (joint pain) | mild pain not interfering with function | moderate pain, analgesics and/or pain interfering with function but not with activities of daily living | severe pain; pain and/or analgesics interfering with activities of daily living | disabling pain |

| **MUSCULOSKELATEL** | | | | |
| --- | --- | --- | --- | --- |
|  | Grade 1 | Grade 2 | Grade 3 | Grade 4 |
| Arthritis | mild pain with inflammation, erythema or joint swelling – not interfering with function | moderate pain with inflammation, erythema or joint swelling – interfering with function, but not with activities of daily living | severe pain with inflammation, erythema, or joint swelling – interfering with activities of daily living | permanent and/or disabling joint destruction |
| Myalgia | myalgia with no limitation of  activity | muscle tenderness (at other than injection site) or with moderate impairment of activity | severe muscle tenderness with marked impairment of activity | frank myonecrosis |

| **SKIN** | | | | |
| --- | --- | --- | --- | --- |
|  | Grade 1 | Grade 2 | Grade 3 | Grade 4 |
| Mucocutaneous | erythema; pruritus | diffuse, maculopapular rash, dry desquamation | vesiculation or moist desquamation or ulceration | exfoliative dermatitis, mucous membrane involvement or erythema, multiforme or suspected Stevens-Johnson or necrosis requiring surgery |
| **Induration** | **< 15mm** | **15-30 mm** | **>30mm** |  |
| **Erythema** | **< 15mm** | **15-30 mm** | **>30mm** |  |
| **Edema** | **< 15mm** | **15-30 mm** | **>30mm** |  |
| **Rash at Injection Site** | **< 15mm** | **15-30 mm** | **>30mm** |  |
| **Pruritus** | **slight itching at injection site** | **moderate itching at injection extremity** | **itching over entire body** |  |

| **RESPIRATORY** | | | | |
| --- | --- | --- | --- | --- |
|  | Grade 1 | Grade 2 | Grade 3 | Grade 4 |
| Cough | transient; no treatment | persistent cough;  treatment responsive | paroxysmal cough; uncontrolled with treatment |  |
| Bronchospasm, Acute | transient; no treatment;  70% - 80% FEV_1_  of peak flow | requires treatment; normalizes with bronchodilator;  FEV_1_ 50% - 70%  (of peak flow) | no normalization with bronchodilator;  FEV_1_ 25% - 50%  of peak flow; or retractions present | cyanosis: FEV_1_  < 25%  of peak flow or intubation necessary |
| Dyspnea | dyspnea on exertion | dyspnea with normal activity | dyspnea at rest | dyspnea requiring oxygen therapy |

| **SYSTEMIC** | | | | |
| --- | --- | --- | --- | --- |
|  | Grade 1 | Grade 2 | Grade 3 | Grade 4 |
| Allergic Reaction | pruritus without rash | localized urticaria | generalized urticaria; angioedema | anaphylaxis |
| Headache | Mild; no treatment required | transient, moderate; treatment required | severe; responds to initial narcotic therapy | intractable; requires repeated narcotic therapy |
| **SYSTEMIC** | | | | |
|  | Grade 1 | Grade 2 | Grade 3 | Grade 4 |
| Fever: oral | 37.7 - 38.5°C or  100.0 - 101.5°F | 38.6 - 39.5°C or  101.6 - 102.9°F | 39.6 - 40.5°C or  103 - 105°F | > 40°C or  > 105°F |
| Fatigue | normal activity reduced < 48 hours | normal activity decreased 25- 50% > 48 hours | normal activity decreased > 50% can’t work | unable to care for self |

| **ORAL** | | | | |
| --- | --- | --- | --- | --- |
| **Oral sites** | Grade 1 | Grade 2 | Grade 3 | Grade 4 |
| Mucosa  (buccal, labial, soft palate, and gingiva) (See Appendix 3 for more detail) | Erythema, and or superficial whitening and wrinkling of epithelium at contact site | Localized maculopapular lesions and or desquamation and ulceration | Diffuse vesiculation or desquamation and ulceration  (Lichenoid reaction) | Severe mucous membrane involvement or erythema, multiforme or suspected Stevens-Johnson or necrosis requiring surgery |
| Tongue | Erythema, altered papilla architecture or loss of papilla on dorsum of tongue | Localized desquamation, or ulceration localized | Diffuse vesiculation desquamation or ulceration  (Lichenoid reaction) | Severe mucous membrane involvement or erythema, multiforme or suspected Stevens-Johnson or necrosis requiring surgery |
| Floor of Mouth | Erythema, and or superficial whitening and wrinkling of epithelium at contact site | Localized desquamation or ulceration | Diffuse vesiculation or desquamation and ulceration  (Lichenoid reaction) | Severe mucous membrane involvement or erythema, multiforme or suspected Stevens-Johnson or necrosis requiring surgery |
| Palate | Erythema and or superficial whitening and wrinkling of epithelium at contact site | Localized maculopapular effects and or desquamation and ulceration | Diffuse vesiculization or desquamation and ulceration  (Lichenoid reaction) | Severe mucous membrane involvement or erythema, multiforme or suspected Stevens-Johnson or necrosis requiring surgery |
| Taste | Transient changes in taste perception  < 1 minute | Altered changes  Metallic, bitter last up to 1 hour | Lasting changes in taste >1 hour | Loss of taste |

